#### Primary outcome analysis

Pain intensity, measured based on the VAS, will be analyzed using a linear mixed-effects model (LMM). Fixed effects will include group, time, group-by-time interaction, baseline VAS score, and rescue medication use. Random effects will account for participant-specific intercepts. Between-group differences at each time point will be estimated with 95% confidence intervals (CIs). A reduction of ≥1.5 points from baseline will be considered clinically meaningful. Pre-planned contrasts will be conducted to test the following hypotheses: (1) the experimental group (YLDJJ + rTMS) will be superior to control group 2 (sham acupuncture + rTMS); and (2) the experimental group will be superior to control group 1 (conventional acupuncture + rTMS). These comparisons will directly test the specific efficacy of YLDJJ acupuncture with those of both a sham control and a conventional acupuncture active control.

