### Relevant concomitant care permitted or prohibited during the trial

#### Permitted concomitant care

Patients will be allowed to receive their regular medications for secondary stroke prevention, including antihypertensive drugs, lipid-lowering drugs, hypoglycemic drugs, antiplatelet drugs, and anticoagulants. The dosages of these drugs will remain stable for at least 4 weeks before randomization and shall remain unchanged throughout the entire trial. Celecoxib will be allowed for emergency pain relief, but the dosage, time, and reasons for its use will be recorded in the patient’s diary in a real-time manner. Routine physical therapy of the hemiplegic limb, including range-of-motion training and stretching exercises, will be allowed as long as it begins at least 1 month before enrollment; however, the frequency and intensity of the treatment will not increase in the trial.

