#### Rescue medication handling

The use of rescue medication (Celebrex) will be quantitatively recorded at each assessment session, incorporated as a covariate in linear mixed models to control confounding. It includes sensitivity analyses excluding high-frequency users (>3 doses/week).

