#### Secondary outcomes analysis

Continuous outcomes (CRPS severity score, FMA, MBI, infrared thermography ΔT, and rs-fMRI connectivity) will be analyzed using the same LMM specification as the primary outcome.

Ordinal outcomes (Brunnstrom stages and MAS) will be analyzed using generalized estimating equations (GEE) with a cumulative logit link function.

Categorical outcomes (e.g., AE adverse event causality) will be compared using *χ*^2^ or Fisher’s exact test.

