#### Exploratory and safety analyses

Blinding success will be assessed using Bang’s BI with 95% CIs. The incidence of AEs will be compared using *χ*^2^ tests, and the severity of AEs will be analyzed via GEE.

Rescue medication use will be included as a covariate in all primary and secondary analyses. Sensitivity analyses will exclude high-frequency users (>3 doses per week).

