#### AE reporting and harms

AE documentation will follow CTCAE v5.0 for all events. Specific procedures for managing common AEs are as follows: For acupuncture, minor bleeding or hematoma will be managed with prolonged local pressure; syncope (needle fainting) will be managed by immediately withdrawing needles, placing the participant in a supine position, and monitoring vital signs. For rTMS, headaches will be managed with rest and non-opioid analgesics if necessary (recorded as rescue medication); in case of a seizure (despite excluding high-risk participants), stimulation will be stopped immediately, standard seizure first aid will be administered, and medical support will be sought. Expected AEs based on the literature and our pilot data include mild (19, 41), transient headache with rTMS (~10 to 15% incidence), and minor local bleeding/bruising with acupuncture (~5 to 10% incidence). For the primary safety analysis, the focus will be on clinically significant risks by including only grade ≥2 (moderate to severe) AEs. Serious adverse events (SAEs) will be events causing death, permanent/significant disability, permanent organ damage, or hospitalization/prolonged stay. In case of SAEs, researchers will immediately ensure participant safety and report it to the sponsor and ethics committee within 24 h. The trial center and blinded editor will jointly perform emergency unblinding due to SAEs. Researchers will determine the need for further treatment using unblinded information.

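### Rescue celecoxib use, recorded after randomisation and prompted by pain, is a covariate in the primary and secondary models, so the treatment effect is estimated with bias

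*Protocol article*

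**What the plan says.** - Primary outcome analysis, on the VAS mixed model: "Fixed effects will include group, time, group-by-time interaction, baseline VAS score, and rescue medication use".
- Secondary outcomes analysis: the continuous outcomes "will be analyzed using the same LMM specification as the primary outcome".
- Exploratory and safety analyses: "Rescue medication use will be included as a covariate in all primary and secondary analyses". The same section plans a sensitivity analysis that drops participants taking more than 3 doses a week.
- Rescue medication handling gives the reason. Rescue use is "incorporated as a covariate in linear mixed models to control confounding", and it "will be quantitatively recorded at each assessment session".
- Table 4 (Outcomes) schedules rescue use at day 10, day 20, 1 month and 3 months. Baseline is not ticked.
- Permitted concomitant care: "Celecoxib will be allowed for emergency pain relief". The section AE reporting and harms also counts non-opioid analgesics taken for rTMS headache as rescue medication.
- Criteria for exclusion from analysis: the primary analysis is intention-to-treat in all randomised participants.

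No described analysis of VAS leaves the covariate out, and rescue use is not listed as an outcome to be compared between arms.

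**The concern.** A confounder influences both allocation and outcome. Here allocation is random, and rescue use comes after it, so the stated reason for adjusting does not apply. Rescue use is a consequence of pain and, if celecoxib works, a cause of later pain. A model that conditions on it compares arms at equal rescue consumption. If YLDJJ lowers pain, its participants also take less rescue, and the model credits part of that difference to the covariate.

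The adjusted coefficient is then not the effect of assignment in all randomised participants. It is not the effect that would be seen without rescue either, because higher pain causes higher use. It answers no clear clinical question, yet both pre-planned contrasts (YLDJJ against sham and against conventional acupuncture) would rest on it.

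The planned sensitivity analysis cannot expose the problem. It selects participants on the same post-randomisation variable and, on the protocol's wording, keeps the covariate in the model. The other planned checks (intention-to-treat against per-protocol, imputed against complete-case, non-parametric alternatives) are not described as dropping it.

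**Working it through.** The protocol gives no rescue rate and no pain-rescue relation, so there is no figure of its own to reproduce. The check asks how far the coefficient moves over a stated range of assumptions.

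**Inputs from the protocol (Sample size; Table 4; Primary outcome analysis).** Difference 1.5 VAS points, SD 1.8, 33 evaluable per arm, three arms, four post-baseline visits, random-intercept model with baseline VAS.

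**Assumptions.** Half the variance lies between participants. The conventional arm has half the YLDJJ effect. Each arm has half its full effect at day 10 and all of it from day 20. Rescue doses per week are R = 1.5 + b × (pain deviation) + noise with SD 1, cut off at zero. Observed VAS = pain − g × R.

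**Algebra, ignoring the cut-off at zero.** Let Δ be the effect on pain without rescue, τ² the noise variance of R, and σ² the variance of pain given the other model terms.

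- Without the covariate: Δ × (1 − g·b).
- With the covariate: Δ × τ² / (τ² + b²σ²). The share lost is the within-arm squared correlation between pain and rescue use. It does not depend on g.

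σ² lies roughly between 1.8² × 0.5 = 1.62 (within-participant) and 1.8² × (1 − 0.5²) = 2.43 (given baseline only). For b = 0.4, g = 0.2:

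- Without: 1.5 × (1 − 0.08) = 1.38.
- With: 1.5 / (1 + 0.16 × 1.62) = 1.19, down to 1.5 / (1 + 0.16 × 2.43) = 1.08.

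**Simulation of the three-arm model** (500 runs per row; YLDJJ minus sham at day 20, shown as benefit):

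| b (doses/week per VAS point) | g (VAS points per weekly dose) | Without covariate | With covariate | Change |
|---|---|---|---|---|
| 0 | 0.2 | 1.50 | 1.50 | none |
| 0.2 | 0.2 | 1.44 | 1.39 | −3% |
| 0.4 | 0.2 | 1.39 | 1.16 | −17% |
| 0.8 | 0.2 | 1.34 | 0.80 | −41% |
| 0.2 | 0.4 | 1.35 | 1.36 | none |
| 0.4 | 0.4 | 1.29 | 1.15 | −11% |
| 0.8 | 0.4 | 1.18 | 0.82 | −31% |

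In the row b = 0.8, g = 0.2, power falls from 0.97 to 0.81. With a true effect of zero and the same rescue behaviour in every arm, both models stay near zero and reject in about 4 to 7% of runs.

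**A second model.** In a simpler two-arm simulation, weekly doses were Poisson with the log-rate rising 0.2 to 0.7 per VAS point, baseline correlation was 0.5, and rescue had no effect on VAS. The estimate moved from about −1.50 to between −1.46 and −1.18, a loss of 0.04/1.50 = 3% to 0.32/1.50 = 21%.

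**The other direction.** Suppose the true effect is zero and one arm takes d extra doses a week for reasons other than pain. The adjusted difference is then −d × bσ² / (τ² + b²σ²). With b = 0.4, σ² = 1.62 and d = 1, this is −0.648/1.259 = −0.51: an apparent benefit with no true effect on pain. A separate simulation of unequal use under a true null gave about −0.4.

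**The exclusion of heavy users.** At the steepest Poisson slope (0.7), excluding those above 3 doses a week removed about 5% of controls and 1% of the YLDJJ arm. Without the covariate, the estimate moved from −1.50 to −1.39 (about 7%). With the covariate kept and a base rate of 0.3 doses a week, it moved from −1.21 to −1.16.

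**The case against.** - **The bias cannot be computed from the protocol.** This stands. It is zero if rescue use is unrelated to pain, negligible in one row of the table, and sensitive to the base rate. In a two-arm rerun, attenuation was about 3 to 18% at 0.3 doses a week and 8 to 30% at 1.0. The percentages are illustrations, not bounds. But rescue is permitted for pain relief, so no link at all is implausible.
- **The flaw is conservative.** This is true only when rescue behaviour at a given level of pain is the same in every arm. If arms differ for other reasons, the adjusted model can show a benefit that is not there.
- **The exclusion of heavy users adds little.** This largely stands. With the covariate kept, it added essentially nothing at slopes 0.2 to 0.5 and only a little at 0.7. Its main weakness is that it cannot reveal the problem.
- **Some rescue use is for rTMS headache.** rTMS is identical in all arms, so this part dilutes the pain-rescue link but does not remove it.
- **Not every analysis can carry the covariate.** The χ² and Fisher tests cannot. The criticism applies to the mixed models and, on the protocol's wording, the ordinal models.
- **Treatment policy is not the only legitimate estimand.** This is correct. When rescue works, the unadjusted estimate also falls below the no-rescue effect (1.18 to 1.44 against 1.5). But it does estimate the effect of assignment with rescue available, which matches the stated intention-to-treat analysis. The adjusted estimate matches neither target.

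**Conclusion.** The concern holds. The protocol fixes a post-randomisation, pain-driven variable as a covariate in its primary model and extends it to the secondary analyses, for a reason that randomisation already answers. This is an explicit specification, not a detail left to an unseen analysis plan. The section Data collection and management requires that plan to be consistent with the protocol.

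If rescue use rises with pain and arms use it alike, the likely result is an understated effect. In the three-arm simulation the loss ran from nothing to about 40%, with power as low as 0.81. If arms differ in rescue use for other reasons, the error can favour the heavier user. These sizes rest on the assumed rescue rate, pain-rescue slope and celecoxib effect. The defect itself does not depend on them. It must be fixed because both pre-planned contrasts depend on this coefficient.

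**What to change.** 1. Remove rescue medication use from the fixed effects in Primary outcome analysis. Delete the matching statements in Rescue medication handling and in Exploratory and safety analyses, so that the secondary models lose the covariate too.
2. Name rescue use as an intercurrent event and state the strategy. Treatment policy, with VAS analysed as observed regardless of rescue, fits the intention-to-treat analysis already planned.
3. Report rescue use (doses per week) by arm as an outcome, so that an arm needing less rescue gets credit for it.
4. Replace the exclusion of participants above 3 doses a week with a sensitivity analysis that keeps everyone. One option is to set VAS values affected by high rescue use to missing and impute them under a stated assumption.
5. If the rescue-adjusted model is kept, label it exploratory. Rescue use may still serve as a predictor in the imputation model.

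The sample size is unchanged, and the rescue data are already scheduled for collection. The cost is a protocol amendment, which under the protocol's own rules needs approval from the study organiser, ethics committee and clinical research centre, and a registry update. It should be made before unblinding.

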#### Outcomes

The efficacy of the intervention will be evaluated by two independent research assistants blinded to group assignment, using pre-specified primary and secondary outcomes. Assessments will be conducted at baseline (before the first treatment), on days 10 and 20, and 1 and 3 months after the end of treatment (Table 4).

**Table 4 tab4:** Schedule of outcome assessments across study time points.

Item	Timepoint				
	Baseline	Treatment period		Follow-up period	
		10 day	20 day	1 month	3 month
Enrolment					
Screening	√				
Signed informed consent	√				
Randomization	√				
Intervention					
Yuan-Luo Da-Jie-Jing acupuncture + rTMS					
Conventional acupuncture + rTMS					
Sham acupuncture + rTMS					
Assessment					
Primary outcome					
VAS	√	√	√	√	√
Secondary outcome					
Brunnstrom	√	√	√	√	√
Modified ashworth	√	√	√	√	√
AROM	√	√	√	√	√
Simplified Fugl-Meyer	√	√	√	√	√
Improved Barthel index	√	√	√	√	√
Infrared thermal imaging	√	√	√	√	√
RS-fMRI	√	√	√	√	√
CRPS-specific severity	√	√	√	√	√
Other measures					
Blinding assessment		√	√	√	√
Additional treatment		√	√	√	√
Rescue medication use		√	√	√	√
Adverse event		√	√	√	√

VAS, Visual Analogue Scale; rTMS, Repetitive transcranial magnetic stimulation; AROM, active range of motion; RS-fMRI, Resting-state functional magnetic resonance imaging.

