#### Primary outcome

Pain intensity will be regarded as the primary outcome. It will be assessed using the visual analogue scale (VAS). The VAS will range from 0 (no pain) to 10 (worst imaginable pain). A reduction of ≥1.5 points will be considered a clinically meaningful improvement (38). The analysis will focus on the mean change from baseline to each time point.

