#### Software and reporting

All analyses will be conducted using R software (v4.5.0) and the packages lme4, mice, and geepack. All results will be reported as statistical estimates with 95% confidence intervals, along with effect sizes for statistically significant outcomes. The false discovery rate will be used for multiple comparison adjustment in secondary outcomes.

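### The random-intercept primary model imposes one variance and one correlation on four unequally spaced visits, so visit-level intervals are miscalibrated if the baseline-adjusted variance or correlation changes over time

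*Protocol article*

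**What the plan says.** All places are in the Protocol article.

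- **Primary outcome analysis**, fixed part: "Fixed effects will include group, time, group-by-time interaction, baseline VAS score, and rescue medication use". Baseline VAS enters once, with no baseline-by-time term.
- **Primary outcome analysis**, random part: "Random effects will account for participant-specific intercepts". No random slope, residual covariance structure, visit-specific variance or robust standard error is stated.
- **Target of inference**: the same section asks for group differences with 95% confidence intervals at every visit. The Primary outcome section agrees: "The analysis will focus on the mean change from baseline to each time point".
- **Outcomes**, visit schedule: "Assessments will be conducted at baseline (before the first treatment), on days 10 and 20, and 1 and 3 months after the end of treatment". With baseline as a covariate, the model has four unequally spaced post-baseline visits.
- **Software and reporting** names "the packages lme4, mice, and geepack".
- **Secondary outcomes analysis**: the continuous secondary outcomes "will be analyzed using the same LMM specification as the primary outcome".
- **Subgroup and sensitivity analyses**: if model assumptions fail, the only stated alternative is non-parametric methods.

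**The concern.** A random intercept with homogeneous residuals is compound symmetry: every visit has the same variance, and every pair of visits the same correlation. Each visit's group difference then takes its standard error from a variance pooled over all four visits. A visit whose true baseline-adjusted variance is above the pooled value gets an interval that is too narrow. A visit below it gets one that is too wide.

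The raw SD need not change for this to happen. If correlation with baseline fades over time, one common baseline slope explains less at later visits, and the residual variance rises even with a constant SD. The named mixed-model package, lme4, has no residual-covariance or visit-specific variance option in its linear mixed model, so the stated software does not relax the assumption.

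At stake is the calibration of each visit-level claim, including the 3-month contrast. The Introduction cites sustained analgesia at 3 months as part of the rationale for YLDJJ. The continuous secondary outcomes inherit the same model.

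**Working it through.** **Inputs from the article.** Two-sided alpha 0.05; SD 1.8 (a single value, from pilot data); difference 1.5; 33 per group before dropout and 42 after; 1:1:1 allocation; four post-baseline visits. No SD or correlation by visit is given, so all such values below are assumptions.

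**The plan's own figure.** Two-group normal formula: n = 2 × (1.96 + 1.2816)² × (1.8/1.5)² = 2 × 10.51 × 1.44 = 30.3, so 31 per group; the exact t calculation gives 32. The stated 33 is close to this, and 33/0.8 = 41.25 gives 42, or 126 in total. (The three-group ANOVA that the article names, with f = 0.42, would need 25. That is a separate matter and does not affect this check.)

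**Formula.** With complete data, the random-intercept model gives every visit contrast the same standard error, based on the mean residual variance over visits. The true error of a nominal 5% test at visit t is therefore about

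size(t) = 2 × [1 − Φ(1.96 × √(mean variance / variance at t))].

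With constant SD 1.8, correlation with baseline ρ(t), and common slope b = mean of ρ(t),

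variance at t = 1.8² × (1 − 2bρ(t) + b²).

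**Worked case.** Assume ρ = 0.7, 0.6, 0.5, 0.4, so b = 0.55 and b² = 0.3025. In units of 1.8²:

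| Visit | 1 − 2bρ + b² | 1.96 × √(0.6975 / variance) | Size |
|---|---|---|---|
| Day 10 | 0.5325 | 2.243 | 2.5% |
| Day 20 | 0.6425 | 2.042 | 4.1% |
| 1 month | 0.7525 | 1.887 | 5.9% |
| 3 months | 0.8625 | 1.763 | 7.8% |

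The mean of the second column is 0.6975. A simulation of 1,000 trials with 42 per group and REML fits gave 2.5%, 4.9%, 6.6% and 8.9%. Its Monte Carlo standard error at 3 months is √(0.089 × 0.911/1000), or 0.9 points.

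**Range of assumptions.** Null simulations used 20,000 trials per scenario, 33 per group, complete data, and the experimental versus sham contrast:

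| Assumed pattern | Day 10 | Day 20 | 1 month | 3 months |
|---|---|---|---|---|
| Equal SD, all correlations 0.5 | 5.2% | 4.9% | 5.0% | 5.4% |
| SD 1.8 throughout, mild decay | 2.9% | 4.3% | 5.9% | 7.6% |
| SD 1.8 throughout, stronger decay (correlation 0.9 per week) | 0.6% | 3.1% | 6.9% | 11.2% |
| SD rising 1.4, 1.6, 1.8, 2.0; correlation 0.5 | 1.6% | 3.6% | 6.1% | 9.1% |
| Mild decay with the same rising SD | 0.6% | 2.5% | 6.9% | 11.7% |
| Mild decay, SD falling 1.8 to 1.5 | 4.5% | 4.8% | 5.1% | 5.1% |
| SD falling 1.8, 1.6, 1.4, 1.2; correlation 0.5 | 9.3% | 6.2% | 3.3% | 1.3% |
| SD peaking at day 20; correlation 0.5 | 2.3% | 9.3% | 5.8% | 3.3% |

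Mild decay means a stable person effect plus a decaying part plus noise. The scenarios repeated at 42 per group (equal, rising and falling SD with correlation 0.5, and stronger decay) gave essentially the same rates.

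**With the assumption relaxed.** A separate variance and baseline slope at each visit, which stands for an unstructured model when data are complete, gave 4.7% to 5.3% at all four visits in every scenario above.

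**The case against.** A random-intercept model is a conventional choice and is correct if compound symmetry is adequate. The documents do not show otherwise. Fading correlation with baseline is a common expectation but not a figure in the article. The VAS is bounded at 0, so later scores could compress as pain falls, which would push the other way. Under moderate assumptions the distortion is small, and at day 20, the end of treatment, it is usually nominal or slightly conservative. The checks use complete data, whereas the plan expects 20% dropout and multiple imputation. Finally, details such as a baseline-by-visit term or the degrees-of-freedom method are often left to an analysis plan.

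Most of this stands as a limit on size and direction. A reader might infer that the planned model makes the day 10 test too strict and the 3-month test too lenient as a matter of course. The documents do not support that. The pattern needs baseline-adjusted variance that grows over follow-up; with equal variance and correlation there is no error, and with a falling SD the pattern reverses.

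The objection does not remove the point. The random-effects form is stated in the article, not left open, and a consistent analysis plan would inherit it. The non-parametric fallback does not address covariance. That the error can run either way is no argument for the pooled variance.

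**Conclusion.** The point holds conditionally. The stated model forces one variance and one correlation on four unequally spaced visits, while the inference is visit by visit. The intervals are miscalibrated if the baseline-adjusted variance or correlation changes across visits.

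Neither size nor direction can be determined from the documents. Under the assumptions tried, the error of a nominal 5% test at 3 months runs from about 1% to about 12%, with 8% under moderately fading correlation and constant SD 1.8. At day 10 it runs from below 1% to about 9%. This is a worthwhile, cheap improvement to the specification. It is not a demonstration that any particular planned test exceeds 5%.

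**What to change.** In Primary outcome analysis, Secondary outcomes analysis and Software and reporting:

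1. Replace the random intercept with an unstructured within-participant covariance over the four post-baseline visits. In R this can be fitted with mmrm, or with nlme::gls using both a general correlation structure (corSymm) and visit-specific variances (varIdent). Visit-specific variances alone are not enough, because repeated visits would then be treated as independent.
2. Add a baseline-by-visit interaction, using the baseline value of the outcome concerned.
3. Prespecify a fallback for non-convergence, for example heterogeneous Toeplitz or heterogeneous AR(1), with robust standard errors.
4. Apply the same form to the continuous secondary outcomes.

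The cost is wording in three sections, one extra R package, and 4 × 5/2 = 10 covariance parameters instead of 2. No extra participants, visits or data are needed.
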